## Method

2

### Design and setting

2.1

The study will be a single-blinded, parallel-group, and randomized clinical trial with an add-on component. The OPC model will be implemented for all participating mothers. Four extra training sessions of 4QM will be provided to mothers in the experimental group. The Ethics Committee of the Iran University of Medical Sciences, Tehran, Iran (IR.IUMS.REC.1400.060) approved the study. It was also registered as a randomized controlled trial (IRCT20140416017301N9) at http://www.irct.ir/.

The study place will be the centers for special learning problems affiliated with Exceptional Education in Tehran. The first author ([name]) will be responsible for the study processes. He is a clinician with experience and an occupational therapist and has experience working with mothers on OPC and 4QM interventions.

### Participants and procedures

2.2

The mothers with DSM-5 diagnostic criteria for SLD will be selected. Participants will be selected through active search in four special learning problems clinics affiliated with Exceptional Education in Tehran, Iran. The children with SLD are those referred to the clinics by public schools.

In the case of children, the inclusion criteria are: (a) age between 7 and 12 years; (b) diagnosed SLD according to the Diagnostic and Statistical Manual of Mental Disorders (5th ed.; DSM–5); (c) not having vision and hearing problems; (d) no comorbid psychiatric disorder according to the Persian version of Child Symptom Inventory-4 (CSI-4); and (e) Intelligence quotient higher than 70 (based on the Persian version of the Wechsler Intelligence Scale for Children-4th Edition (WISC-IV). Cases with significant symptoms according to CSI-4 will be referred to a psychiatrist.

In the case of mothers, the inclusion criteria will be age range of 25–50 years and a high school diploma at least. Mothers who are in charge of caring for another person with disabilities, or severely depressed (Depression, Anxiety, and Stress Scale-21 [DASS-21]) will be excluded [48].

To assess eligibility criteria, mothers of children with SLD will be interviewed and advised regarding the type of study. Selected mothers will need to sign an informed letter of consent. An external examiner with training (an occupational therapist) will examine the children and their mothers using CSI-4 and DASS-21 respectively. In addition, a psychologist will examine children using WISC-IV (Fig. 1).

**Fig. 1 fig1:**
[figure not shown]
Flowchart of the study.

### Participant timeline

2.3

Participant timelines initiate eligibility screening through allocation, pre/post-intervention, intervention, and follow-up (Fig. 2).

**Fig. 2 fig2:**
[figure not shown]
Schedule of enrolment, interventions, and assessments.

### Sample size

2.4

Sample size calculations were performed in G-Power software based on the COPM test as the main variable of the study. A two points change in this variable between the intervention and control group will be considered as significant difference [49]. Considering α-value of 5%, the power of 95%, the standard Cohen's effect size of 1, the required sample size was obtained equal to 27 for each group, and assuming 10% dropout rate, 30 subjects were selected for each group. Furthermore, since the sample size was calculated based on the primary outcome, the study is anticipated under-powered for addressing secondary outcomes.

### Allocation

2.5

Mothers of children with SLD with the inclusion criteria will be assigned with a number. After baseline assessment, the research coordinator will allocate them sequentially (allocation ratio 1:1) to the control or experimental group, based on the random numbers generated by *randomization. com*.

### Blinding

2.6

In this study, two occupational therapists will support the experimental and control groups. Therefore, given the nature of the therapeutic intervention, the participant (mother) cannot be blinded about their grouping. To decrease participants’ bias, the study hypotheses will not be communicated. Examiner will be kept blinded about allocation of the participants and the order of the assessment. Additionally, data input will be done by a research assistant without a direct role in the intervention. Group allocations will not be revealed to data analysts.

## Interventions

3

First, necessary explanations about the importance of OPC or OPC+4QM for participation in outside school activities in SLD children will be given to the mothers. To ensure adherence and compliance to treatment, an evaluation form to assess mothers' ability to implement the instruction of each session and important issues during the intervention course will be completed by each participant. Mothers will not be required to quit other interventions, if any, such as psychology or their child's school tutorials; however, they need to avoid engaging in other occupational therapy interventions.

Second, the original OPC (Graham & Rodger, 2010) and 4QM (Greber, 2007) protocols will be used in the study groups [39,50]. Two occupational therapists who have more than 5 years of experience working with mothers with children with neurodevelopmental disorders will conduct the interventions, and both OPC and 4QM protocols are available through manuals. A rater will be present during the intervention sessions in both experimental (OPC+4QM) and control (OPC) groups and complete the occupational performance fidelity measure (OPC-FM) to observe the principles of OPC by the therapist and also to check the quality of behavior of the mothers [[51], [52]]. OPC-FM consists of 18 items, and a higher score indicates a better OPC behavior. The average score will be 34.1/45 for the first session and 41.3/54 for the other sessions. The minimum requirement recommended in the coaching manual will be 80% fidelity in every session [51].

Third, all the participating mothers will be provided with a booklet for the study based on prior experiences containing information related to OPC and an additional part about implementing the 4QM approach and guided discovery to help the improvement of participation in activities outside school-related to their children.

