**Method:**

A single-blinded, parallel-group randomized clinical trial will be carried out. Mothers of children with SLD will constitute the participants and be allocated to experimental (OPC+4QM) and control (OPC alone) groups.

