### 4QM protocol

3.2

The OPC+4QM interventions will be provided once a week with fourteen 60-min sessions (ten sessions for OPC + four sessions for 4QM). The follow-up period will be one month. Four sessions of 4QM will be scheduled in four quadrants during the OPC sessions to achieve the identified goals. After analyzing each goal in the OPC approach by using collaborative performance analysis, 4QM will be employed for the plan action of that goal. Also, the principles of teaching and learning will be present both in OPC and 4QM sessions, but in Four sessions of the 4QM, various cognitive and physical learning strategies are organized and implemented in the form of 4 quadrants.

The first 4QM intervention sessions along with the first OPC session introduce the 4QM, its components, and presents the printed forms of 4QM for each goal to the mothers. The second, third, and fourth sessions of 4QM interventions will be done along with the OPC sessions related to the first to third selected goals to train and implement the goals in the format of 4QM.

Integration of two continua is used in 4QM given the (i) directness of the strategy (first direct and then indirect) and (ii) clustering the initiation source (first the mother as a facilitator and then the child as a learner) to prompt teaching-learning strategies given the needs of the child. In the quadrant 1, the characteristics and requirements of the task are determined. Strategies including demonstration, explicit instruction/explanation, lower-order questions, and physical patterning, will be initiated by the mother (facilitator) directly. In the quadrant 2, the child will be supported in carrying out tasks through involving them in decision-making processes. Indirect strategies including feedback, higher-order questions, nonverbal prompts, physical prompts, and think-aloud modeling will be initiated by the mother (facilitator). The quadrant 3 will focus on identifying the steps of the activity and child (learner) driven processes and highlights direct strategies like mnemonics, priming, visual cues, verbal self-instruction, and kinesthetic self-prompting that a child (learner) might overtly use to improve their performance through concentrating on key points. Quadrant 4 indicates autonomous performance by the child (learner) through indirect strategies like self-instruction, self-questioning, mental imagery, problem-solving, self-monitoring, and automaticity [44,55,56] (Table 2).

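### As written, the booklet for all mothers includes a part on implementing 4QM, which conflicts with an OPC-alone control and may dilute the contrast under test

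*Protocol article*

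**What the plan says.** The Method paragraph of the abstract says that mothers will "be allocated to experimental (OPC+4QM) and control (OPC alone) groups". Design and setting (2.1) describes an add-on design: "The OPC model will be implemented for all participating mothers", and then "Four extra training sessions of 4QM will be provided to mothers in the experimental group". The 4QM protocol (3.2) places the four sessions within the OPC+4QM programme, and its first session "presents the printed forms of 4QM for each goal to the mothers".

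Interventions (section 3) then says that "all the participating mothers will be provided with a booklet for the study", "containing information related to OPC and an additional part about implementing the 4QM approach and guided discovery". No sentence there or elsewhere in the article limits the 4QM part to the experimental arm or mentions a separate control version.

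**The concern.** The comparative question is what 4QM adds to OPC, so the contrast depends on controls not being taught 4QM. The booklet sentence, followed as it stands, gives them written guidance on carrying it out. This is not a remote route of exposure. Under 3.2 and Table 2 the mother initiates the strategies of quadrants 1 and 2, and the Introduction says that plans are carried out at home and in the community. The booklet therefore reaches the person who would apply the method, in the place where it would be applied.

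The sample-size calculation makes no allowance for such exposure. The one fidelity measure named in section 3, the OPC-FM, covers OPC principles, so the article describes nothing that would show whether control mothers used 4QM.

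**Working it through.** **1. Do the passages conflict?**

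- Control: OPC alone (abstract).
- Planned difference between arms: four additional 4QM sessions, experimental arm only (2.1 and 3.2).
- Booklet: all mothers, with a 4QM implementation part (section 3).

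Section 2.1 uses almost the same all-mothers phrase for what both arms receive, and names the experimental group when it means one arm. Section 3 itself names the two groups separately one paragraph before the booklet sentence. The literal reading is therefore that both arms get the whole booklet, which conflicts with the abstract's control.

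**2. How much of 4QM would reach controls?** Only the written part. The sessions and the per-goal forms belong to the OPC+4QM programme. Guided discovery is listed as OPC content in 3.1 (item f of the information-exchange domain), so that half of the booklet's additional part is legitimate control material. The remaining exposure is the 4QM text.

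**3. Reproducing the planned sample size.** Inputs from Sample size (2.4): α = 5%, power 95%, Cohen's d = 1, target difference 2 COPM points. The implied SD is 2 / 1 = 2 points. Allocation is 1:1 (2.5). Two-sided testing is taken from Statistical methods (5.3), because 2.4 does not state it. The two-sample t test (noncentral t) gives 26.99, so 27 per arm, with power 0.950. Dropout: 27 / 0.90 = 30. Both stated figures reproduce.

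**4. Effect of dilution.** Let f be the share of the 4QM effect that reaches controls through the booklet. Then:

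- difference = 2 × (1 − f) points
- d = 1 − f
- noncentrality = d × √(n/2), with 2n − 2 degrees of freedom

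For example, f = 0.25 with n = 27 gives 0.75 × √13.5 = 2.756 on 52 degrees of freedom, and power 0.772.

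| Assumed f | Difference (points) | d | Power, 27 per arm | Power, 30 per arm |
|---|---|---|---|---|
| 0 | 2.0 | 1.00 | 95.0% | 96.8% |
| 10% | 1.8 | 0.90 | 90.1% | 92.9% |
| 25% | 1.5 | 0.75 | 77.2% | 81.5% |
| 50% | 1.0 | 0.50 | 43.8% | 47.8% |

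The 30-per-arm column applies if nobody drops out. The documents give no value for f. The three non-zero rows are assumptions chosen to show a range.

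**The case against.** The strongest reply is that the sentence is loosely worded. Calling the 4QM content an additional part may describe a supplement for the add-on arm, compressed into one sentence of a condensed article. The rest of section 3 keeps the arms apart, and 3.2 places 4QM training with the experimental arm. This is a plausible account of what was intended, and it rules out treating it as established that controls will receive 4QM material. It does not remove the point: the sentence says all mothers, a team following it would hand the part to controls, and a reader cannot tell what controls received.

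A reader might go further and infer that the control arm receives the experimental intervention, so that a null result would be uninterpretable. The documents do not support that. Section 2.1 identifies the add-on as four training sessions, and controls do not get them. Nor do they get the per-goal forms used after collaborative performance analysis. If both arms held the booklet, the randomised comparison would still estimate the effect of adding the 4QM sessions and forms to OPC with the booklet. That is narrower and possibly attenuated, but meaningful. A positive result would not be undermined, because the bias runs towards no difference.

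It is also fair to object that no transfer fraction can be taken from the documents. At 10% the loss is modest: 90.1% power at 27 per arm and 92.9% at 30. None of the figures is an estimate of what will happen.

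**Conclusion.** The point holds as a conflict within the document that bears on the trial's one planned contrast. On its literal wording, section 3 gives controls written 4QM instruction, contrary to the abstract's definition of the control and to 4QM's role as the only add-on. Exposure would be partial. If 4QM is effective and control mothers use the material, the difference is biased towards zero, and a null finding would be ambiguous between no benefit and a diluted comparison.

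The size is unknown. Over assumed transfers of 10% to 50%, power at 27 per arm lies between 90% and 44%, against the planned 95%. This rests on the implied SD of 2 points, a two-sided 5% t test and a proportional loss of effect. Whether controls would in fact be given the 4QM part is uncertain, because the authors may have intended otherwise. On either reading the sentence needs correcting, and the exposure cannot be undone once booklets have been handed out.

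**What to change.** Reconcile the booklet sentence in section 3 with the abstract, 2.1 and 3.2 by stating which arm receives which booklet content. If the control is OPC alone, print two versions: controls receive one without the 4QM part, and only mothers allocated to OPC+4QM receive the 4QM part. Guided discovery can stay in both, since 3.1 lists it under OPC. The printed 4QM forms need no change, as 3.2 already places them in the 4QM sessions.

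Optionally, add an item on any use of 4QM material to the evaluation form that section 3 already asks each mother to complete, so that contamination can be reported. This is preferable to having the session rater tick off quadrant strategies in control sessions. Such a list could flag ordinary OPC teaching and problem-solving as contamination, and would miss use of the booklet at home.

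The cost is a second booklet version and, if adopted, one extra form item.

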### OPC approach protocol

3.1

OPC interventions will be delivered for ten 60-min sessions provided once a week. The follow-up period will be one month.

In the first session, after introduction and explanation about the details of the OPC interventions, five goals related to the child's participation in activities outside school (three trained and two transfer goals) will be set by each mother for her child. In the second session, the problem-solving process will begin for the first goal and the printout of the problem-solving process will be given to the mothers. In this session, the mother will be asked to carry out two different actions at least about the desired goal during the next session. In the third session, the first goal will be reviewed and the work on the second and third goals (one or two for each goal) will begin. In the fourth to eighth sessions, progress will be reviewed across the three goals. In the ninth session, the selected goals will be reviewed and the necessary points for the end of the intervention sessions will be discussed. In the tenth session, which is the last session and the end of OPC intervention, a decision is made about the goals that were not achieved. Transfer goals (fourth and fifth goals) will also be implemented by mothers during the follow-up period.

The content of the sessions is based on enabling principles that include three domains: emotional support, information exchange, and structure of the process. The emotional support domain is focused on listening to parents' information and interpretation by the child. The fundamental facilitating actions in this domain are motivators for change, learning needs in implementing change, previous success in enabling performance, expressing empathy, assisting parents in reframing their perceptions of the child, enabling performance and guiding parents’ reflections and choices of action, encouraging persistence, and future independent problem-solving. In the information exchange domain, a discussion takes place between the mothers and the therapist regarding (a) collaborative performance analysis, (b) understanding typical development, (c) impairments and related challenges in children with SLD, (d) teaching and learning strategies, (e) finding and accessing community resources, and (f) implementation of guided discovery in different settings. In the structured problem-solving process, priority goals related to activities outside school that are chosen by the mother and indicate worries about her child will be discussed by the therapist and the mother and explore options will be examined. Then, the actions are planned and the results will be checked [39,53,54] (Table 1).

**Table 1 tbl1:** Coaching protocol based on OPC principles.

OPC domains	Key facilitating actions
Emotional Support	• Listen
	• Emphasize
	• Reframe
	• Guide
	• Encourage
Information Exchange	• Collaborative performance analysis
	• Typical development
	• Health conditions and impairments
	• Teaching and learning strategies
	• Specialized Strategies
	• Community resources and Entitlements
Structure the Process	• Set Goals
	• Explore Options
	• Plan Actions
	• Carry out Plan
	• Check Performance
	• Generalize

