### Goal setting

3.3

Mothers need to speak about their child's activities outside school and to set three objectives for the intervention and two extra goals (transfer goals) as the measure of outcome for the transfer [41]. The occupational therapist will ask mothers to assign a point to each goal with the 10-point scale scoring system of the COPM (Canadian Occupational Performance Measure). To make mothers more familiar with the details of activities outside school, during the semi-structured interview COPM, CPAS-P (Children Participation Assessment Scale -Parent Version), including 71 items of different areas of children's occupational performance will be provided to them. In addition, simultaneous with the COPM, the Goal Attainment Scale (GAS) will be used to examine the achievement of the desired goals.

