##### Transfer of skills

4.2.1.4

The transfer goal (fourth and fifth goals) will not be covered in the intervention. The occupational satisfaction and performance in the children on the transfer goal will be measured using COPM's scoring system. Furthermore, achievement of these objectives will be measured using GAS at baseline, post-intervention, and after a 1-month follow-up. Capistran and Martini reported the use of extra goals to evaluate transfer with children [70].

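### The protocol contradicts itself on when COPM and GAS goals are set and first scored: before allocation, or in the first treatment session after it

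*Protocol article*

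**What the plan says.** **When goals are set.** Section 3.1 (OPC approach protocol) gives the only date: "In the first session, after introduction and explanation about the details of the OPC interventions, five goals related to the child's participation" are set. They are split there and then: "three trained and two transfer goals) will be set by each mother for her child". Table 1 lists goal setting as an OPC action.

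**When allocation happens.** Section 2.5 (Allocation): "After baseline assessment, the research coordinator will allocate them sequentially (allocation ratio 1:1) to the control or experimental group". No instrument is named.

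**What is analysed.** Section 4.2.1.4 (Transfer of skills) has attainment of the transfer goals "measured using GAS at baseline, post-intervention, and after a 1-month follow-up". Section 5.2 (Data analysis) takes COPM and GAS as change from baseline t1 to t2 and t3, for trained and for transfer goals. Section 2.4 sizes the trial on COPM.

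**Who takes the scores.** Section 3.3 (Goal setting), which stands under Interventions: "The occupational therapist will ask mothers to assign a point to each goal with the 10-point scale scoring system of the COPM". GAS is used at the same time. Section 2.6 says that two occupational therapists deliver the programmes, that mothers cannot be blinded, and that the examiner is. Section 4.2 says that the blinded assessors are occupational therapists too.

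**What the experimental arm receives at that time.** Section 3.2 (4QM protocol): "The first 4QM intervention sessions along with the first OPC session introduce the 4QM", with printed forms for each goal.

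**The concern.** COPM and GAS are individualised. The items are the goals the mother chooses, and there is nothing to rate until they are chosen. Setting the goals in treatment session 1 therefore puts the first possible rating after allocation, whereas the allocation and analysis sections treat baseline as something already complete.

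If the session 1 timing is what happens, four things are decided after the mother knows her arm: which goals are chosen and how hard they are, which three are trained and which two are transfer, what counts as the expected level on GAS, and the starting scores. She may by then have heard arm-specific explanation, because Section 3 opens with an explanation of the assigned programme and 4QM is introduced alongside OPC session 1.

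Randomisation balances what is fixed before it, not a goal set or starting score produced after it. At stake is the interpretability of the between-arm comparison on the variable that sizes the trial, and on GAS and the transfer goals as well.

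**Working it through.** **1. The sequence**

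| Step | Section 2.5 with 4.2.1.4 and 5.2 | Section 3.1 with 3.3 |
|---|---|---|
| Goals chosen | must precede t1 (implied) | treatment session 1 |
| COPM/GAS t1 scores | baseline assessment | session 1 at the earliest |
| Allocation | after baseline | before session 1 |
| Mother knows her arm | after t1 | before t1 |

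Both columns can be true only if the baseline assessment of Section 2.5 leaves out COPM and GAS. In that case the t1 of Section 5.2 is a post-allocation measurement for these two scales.

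**2. The plan's own sample size**

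Inputs from Section 2.4: α = 5%, power 95%, d = 1, dropout 10%. Two-sided testing is stated in Section 5.3. The two-sample t test (noncentral t) gives n = 26.99, so 27 per group, with power 0.950 at 27; the normal approximation gives 26. Dropout: 27 / (1 − 0.10) = 30. The stated figures reproduce, so the sample size itself is not in question.

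**3. Why adjustment for t1 does not repair it**

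Suppose the experimental arm's t1 ratings are lowered by δ and nothing else changes.

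- Change score: bias = δ.
- Baseline-adjusted comparison with within-arm slope β on t1: adjusted difference = (difference at t2) − β × (difference at t1) = 0 − β × (−δ) = βδ. This is zero only if β = 0.

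A shift in goal difficulty is different. An easier goal may raise both t1 and t2, and its net effect on change could go either way.

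**4. Illustration of size**

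Assumptions:
- SD = 2 points / d of 1 = 2, taken to apply to the analysed change score.
- No true effect, a single two-sample t test, two-sided 5%.
- A net spurious shift s in the change score. The documents give no value for s.

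Noncentrality = (s / 2) × √(n / 2). For n = 30: √15 = 3.873, df = 58, critical value 2.002.

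| Net shift s | s / SD | Noncentrality (n = 30) | Rejection, 30 per arm | Rejection, 27 per arm |
|---|---|---|---|---|
| 0 | 0 | 0 | 5.0% | 5.0% |
| 0.25 | 0.125 | 0.48 | 7.6% | 7.4% |
| 0.5 | 0.25 | 0.97 | 15.9% | 14.7% |
| 1.0 | 0.5 | 1.94 | 47.8% | 43.8% |

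For any fixed shift the false-positive rate rises with n, so a larger trial makes it worse.

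**The case against.** The best defence is that Section 2.5 does state the right order and that Sections 4.2.1.4 and 5.2 speak of a baseline. Goals might be elicited in a baseline COPM interview and only taken up again in session 1. The schedule in Fig. 2, which is not shown here, might say so. Four stronger readings should therefore be resisted.

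- **That the primary outcome has no pre-randomisation baseline.** A reader might infer this from Section 3.1, but Section 2.5 says otherwise in general terms. What stands is a contradiction. A figure listing COPM at baseline would not remove it, because the session 1 wording would still conflict.
- **That the treating therapist scores the outcome and breaks the blind.** Section 3.3 does not say which occupational therapist it means, and the assessors share that profession. The session setting makes the treating therapist a natural reading, but the text is ambiguous rather than contradictory.
- **That the 4QM introduction steers goal choice.** Section 3.2 places it alongside session 1 but does not say that it precedes goal selection. Forms for each goal, and use of 4QM after each goal is analysed, suggest that the goals may come first. Exposure is possible, not shown.
- **That all primary outcomes are affected.** CPAS-P does not depend on the chosen goals and can be completed before allocation.

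There is some mitigation: hypotheses are withheld from mothers, mothers rather than therapists choose the goals, and the CPAS-P item list is offered as a prompt during the goal interview. None of this settles when t1 is taken. Finally, goal setting belongs to OPC, and Section 3 requires 80% fidelity in every session, so moving it touches session 1 content and is slightly more than an edit.

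**Conclusion.** The concern holds as an internal contradiction with a consequence. Sections 2.5, 3.1, 3.3, 4.2.1.4 and 5.2 cannot all be followed as written for COPM and GAS. If Section 3.1 governs, goal choice, the trained/transfer split, GAS level 0 and the t1 scores are post-randomisation, set by an unblinded mother, and open to bias that neither adjustment for t1 nor a larger sample removes. COPM, which sizes the trial, and GAS are exposed, on trained and transfer goals alike.

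The size cannot be derived from the documents. The figures of about 16% and 48% rest on assumed net shifts of 0.5 and 1 point, an SD of 2 inferred from Section 2.4, and 30 analysed per arm. They describe a net shift in the change score, such as one confined to t1, and are not a forecast. The matter should be settled before enrolment, because goals set after allocation cannot be re-set in the analysis.

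**What to change.** - **Section 2.5:** state that the baseline visit includes the COPM/GAS interview with the blinded examiner. It fixes the five goals, the trained/transfer split, the GAS level descriptors and the t1 scores. The goal sheet is locked before allocation.
- **Section 3.1:** let session 1 review and work from the locked sheet, so that the OPC goal-setting component is retained.
- **Section 3.3:** replace the unspecified occupational therapist with the blinded assessor, who collects COPM and GAS at t1, t2 and t3.
- **Fig. 2:** check that it shows the same order.

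**Cost.** The interview moves to a visit and an examiner that the plan already has. Sample size and number of sessions stay as they are. The small downside is that the treating therapist is not part of the first goal interview, and session 1 reviews the goals rather than first setting them; the fidelity rating of that session should allow for this.

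**What it does not solve.** The mother still rates COPM at t2 and t3 knowing her arm, whoever asks the questions. That rating bias remains and should be acknowledged.
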